##### Body fat percentage measurement

Dual-energy X-ray absorptiometry (GE Lunar Prodigy, software version 10.51.006, GE Healthcare, Madison, United States) will be used to measure body fat percentage. Each participant will be scanned in the supine position using X-rays at two energy sources (40 keV and 70 keV) in fast mode. A series of transverse scans will be performed from head to toe at 1 cm intervals. The time spent will be approximately 5 min, depending on the participant’s height.

#### Secondary outcome measures

##### Postural stability assessment

Postural control during daily living activities is regulated by the horizontal center of mass acceleration, which is mainly associated with the horizontal distance between the center of mass and center of pressure from a biomechanical perspective. The postural instability associated with obesity usually results in altered biomechanics strategies designed to improve the person’s sense of balance during locomotion [13]. Therefore, three-dimensional motion analysis will be used to measure kinematics and kinetics data, as well as to evaluate dynamic postural stability during different tasks.

Kinematics and kinetics data will be collected and analyzed using a Vicon Motion Analysis System (Vicon MX-13, Oxford Metrics, UK) with nine infrared cameras that record three-dimensional motion at 200 Hz and coupled with force plates (models 9286AA, Kistler Instruments Corp, Swaziland) that record ground reaction force at 1,000 Hz. The trajectories of 45 retro-reflective markers (14 mm in diameter) will be captured at different landmarks of the subject according to a Plug-in-Gait marker set.

These biomechanical data will be collected while each participant performs three tasks:Level walking at normal speed, faster speed, and slow speedNormal cadence is the subject’s preferred speed. Fast speed is 30% faster than the normal walking speed, and slow speed is 10% slower than the normal walking speed [11]. Four force plates will be embedded on the ground in the middle of a walkway, so that the participants can plant their feet on each plate consecutively during walking.Stair climbingThe experimental staircase consists of six steps. The step dimensions are 17 cm (height) and 28 cm (tread) with a stair slope of 31° [33]. No handrail will be used. Three force platforms (9286AA, Kistler Instruments Corp, Switzerland) are embedded in the second, third, and fourth steps of the staircase. The participants will be asked to walk, ascend, and descend at their natural speed without any reference to the force platforms.Rising from a seated positionDuring the task, the participants will rise from a seated position from a 30 cm high bench. They will be instructed to sit on the edge of the bench, with each foot on a force plate equidistant from the center line, and to bend their knees so that their feet are slightly behind their knees [10].Static posture stability will be examined during the double-leg stance and tandem stance with eyes open and closed [11]. The subjects stand with two heels touching together and the feet externally rotated by 10° in the double-leg stance. The subjects stand with the dominant foot forward from heel to toe in the tandem stance. The center of pressure data will be collected from a force platform (9286AA, Kistler Instruments Corp, Switzerland) using BroWare data collection and analysis software with a sampling frequency of 1,000 Hz in a computer workstation. The subjects will be asked to stand as still and as quietly as possible with arms akimbo and barefoot to eliminate the effects of shoes, socks, and heel height. The required standing time is 30 s. If the participant loses balance in the period (steps to regain balance), he or she will be asked to repeat the test up to a maximum of three times. A 3 min rest will be allowed between two tests. The center of pressure displacement in the medial-lateral and anterior-posterior directions will be used to analyze postural stability.

##### Proprioception test of knee and ankle

This measurement method was reported in our previous studies [15]. Knee and ankle proprioception will be tested using an electrically driven movable frame. During the tests, the participant will sit on a chair with the dominant leg supported by the frame. The leg can be passively moved in a flexed or extended direction at a velocity of 0.4°/s. Once the participant is able to detect the leg motion, he or she will press a handheld stop button and confirm the direction of the motion. The rotation angles of the frame will be determined as the threshold for the detection of the knee and ankle joint. The mean values of the three trials in one direction will be used for the analysis.

##### Neuromuscular response

Neuromuscular response indicated by muscle latency will be assessed using electromyography (EMG) of the leg muscles while an unexpected perturbation is applied to the ankle. A customized trapdoor with an 18° tilt angle will be used to generate an ankle inversion perturbation while subjects stand barefoot on the trap doors. The Noraxon EMG system (Noraxon USA Inc., Scottsdale, USA) will be used to collect surface EMG signals from five muscles (rectus femoris, semitendinosus, gastrocnemius, peroneus longus, and anterior tibialis) of the right leg and onset signals at the trapdoor tilting with a sampling frequency of 1,000 Hz. Both feet will be randomly tilted at least seven times to decrease anticipatory effects. The onset latency of the muscles refers to the time interval in milliseconds (ms) between the trapdoor initiation and the first rising front of the EMG burst from the baseline. The EMG onset will be visually determined by an experienced researcher.

Furthermore, muscle activation will be determined during level walking and stair climbing. The EMG data will be collected from eight lower extremity muscles according to the recommended muscles for gait analysis from Winter and Yack [34]; these muscles are the ipsilateral and contralateral erector spinae at the level of the iliac crest, rectus femoris, vastus medialis, vastus medialis, tibialis anterior, biceps femoris, peroneus longus, and gastrocnemius. The Noraxon EMG system (Noraxon USA Inc., Scottsdale, USA) will be used to collect surface EMG signals from these muscles of the right leg with a sampling frequency of 1,000 Hz. The EMG signals from five complete gait cycles per task will be used in data reduction. Prior to the EMG data collection, maximal isometric contraction data will be gathered for each muscle. The mean EMG amplitude and on-off muscle timing during a gait cycle will be used in the data analysis [35].

##### Muscle strength test of knee and ankle

Muscle strength of the dominant knee and ankle joint will be tested using an isokinetic dynamometer [17]. Participants will perform three maximum concentric contractions for the knee extensors and flexors at an angular velocity of 60°/s. The highest peak torque that indicates muscle strength will be normalized by kilogram of body weight. The dynamic endurance of the knee extensors and flexors will be assessed by measuring 40 repeated maximum isokinetic contractions at an angular velocity of 180°/s. The work in moving from a knee angle of 80° to a knee angle of 10° will be recorded for each contraction. The endurance index is defined as the ratio of the work performed during the last five contractions over the first five contractions. Ankle dorsiflexor and plantarflexor strength will be measured at an angular velocity of 60°/s. Participants will be instructed to push a foot away from themselves and then pull it toward themselves at the maximum velocity for each action. Peak torque will be determined as the highest torque generated from the three trials. Relative peak torque will also be analyzed (Figure 1).

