**Methods/design:**

We will conduct a prospective, single-blind, randomized controlled trial with 120 prepubescent obese children. Participants will be randomly assigned to a weight management group or a control group. The weight management group will participate in a dietary and exercise program. The control group will receive health education. After the intervention, participants will be followed for 6 months with no active intervention. The primary and secondary outcomes will be assessed at the baseline, and after 6 months and 12 months. Primary outcome measures will include body weight, body height, body mass index, waist circumference, hip circumference, and body fat percentage. Secondary outcome measures will include three-dimensional functional biomechanics in different tasks, proprioception tests of the knee and ankle, neuromuscular response of the leg muscles, and muscle strength tests of the knee and ankle. Furthermore, adverse events will be recorded and analyzed. An intention-to-treat analysis will be performed if any participants withdraw from the trial.

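### As most naturally read, the protocol analyses knee strength only per kilogram of body weight, which the programme aims to change, so a weight difference alone would raise the knee measure

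*Protocol article*

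**What the plan says.** The protocol article lists strength among the secondary outcomes: "neuromuscular response of the leg muscles, and muscle strength tests of the knee and ankle". Its section on the muscle strength test then takes the two joints in turn.

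- **Knee strength.** Children perform three maximal concentric contractions at 60°/s. The variable is defined by the sentence "The highest peak torque that indicates muscle strength will be normalized by kilogram of body weight".
- **Knee endurance.** "The endurance index is defined as the ratio of the work performed during the last five contractions over the first five contractions". Body weight does not enter this index, but it describes fatigue, not strength.
- **Ankle.** "Ankle dorsiflexor and plantarflexor strength will be measured at an angular velocity of 60°/s". After the instructions for the ankle movement come two closing sentences: "Peak torque will be determined as the highest torque generated from the three trials" and "Relative peak torque will also be analyzed".

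The denominator of the knee variable is itself a primary outcome: "Primary outcome measures will include body weight, body height, body mass index, waist circumference, hip circumference, and body fat percentage".

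The Statistical analysis section specifies a linear mixed model with time, group and their interaction. The potential covariates, weight status among them, are those determined at baseline.

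**The concern.** The knee variable is a ratio, and its denominator is measured after randomization and targeted by the treatment. If the programme works on weight, torque per kilogram rises in the treated arm even when the muscle produces the same torque. Absolute weight loss is not needed. These are growing children, so slower weight gain than in the control arm has the same effect.

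The trial's title and aim concern neuromuscular function, and the Discussion presents its measurement as a way to explain the mechanism of postural instability. A knee result available only per kilogram could not show whether muscle strength changed or whether part of the primary weight result had reappeared in another form. It could also hide a loss of strength, which is a result one would want to see in a diet and exercise trial.

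**Working it through.** The document gives no expected weight difference, standard deviation, correlation or power for this outcome, so there is no figure of its own to reproduce.

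**Inputs from the document.** 120 children allocated 1:1, so 60 per arm; knee strength as torque T divided by weight W.

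**Assumptions.** Between-arm weight difference w of 3%, 5% or 8%; between-child CV of torque per kilogram of 20% (range 15% to 25%); correlation r between baseline and follow-up of 0.8 or 0.6; two-sided alpha 0.05; no dropout.

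**Step 1: apparent gain with unchanged torque.** Gain = 1/(1 − w) − 1.

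- w = 3%: 1/0.97 − 1 = 3.1%
- w = 5%: 1/0.95 − 1 = 5.3%
- w = 8%: 1/0.92 − 1 = 8.7%

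The corresponding effect on absolute torque is 0% in each case.

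**Step 2: growing children.** Suppose torque rises 6% in both arms, while weight rises 6% in control and 1% in the programme arm. The ratio of torque per kilogram between arms is (1.06/1.01)/(1.06/1.06) = 1.050. That is a 5.0% advantage with identical torque growth and no child losing weight.

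**Step 3: masking.** If absolute torque falls by a fraction x, the ratio changes by the factor (1 − x)/(1 − w), which stays at or above 1 whenever x ≤ w. At a 5% weight difference, a torque loss of up to 5% would not show as a fall.

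**Step 4: does the stated model remove it?** No. Baseline weight status is fixed before treatment starts and cannot account for a treatment effect on later weight.

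**Step 5: chance that the effect alone is significant.** Two-sample t test, 60 per arm, with standardized difference d:

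- unadjusted: d = gain/CV
- adjusted for baseline: d = gain/(CV × √(1 − r²))
- change from baseline: d = gain/(CV × √(2(1 − r)))

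For w = 5% and CV 20%, d is 0.0526/0.20 = 0.26 unadjusted, and 0.0526/(0.20 × 0.6) = 0.44 adjusted with r = 0.8. For change scores d is 0.0526/(0.20 × 0.632) = 0.42 with r = 0.8, and 0.0526/(0.20 × 0.894) = 0.29 with r = 0.6.

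| Analysis (CV 20%) | w = 3% | w = 5% | w = 8% |
|---|---|---|---|
| Unadjusted | 13% | 30% | 66% |
| Change score, r = 0.6 | 16% | 36% | 75% |
| Change score, r = 0.8 | 26% | 62% | 96% |
| Adjusted for baseline, r = 0.8 | 29% | 66% | 98% |
| Change score, r = 0.8, Bonferroni for an assumed three comparisons | 14% | 44% | 91% |

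At w = 5%, moving the CV from 15% to 25% takes the unadjusted figure from 48% to 21%, and the baseline-adjusted figure (r = 0.8) from 89% to 48%.

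**The case against.** **Absolute knee torque may be intended.** A reader might infer that the protocol rules it out. No sentence says so. The section heading covers both joints, and the only count of three given earlier in the section belongs to the knee, so the closing sentences on peak and relative torque could apply to both. This reading is possible but less natural: the sentences follow directly on the ankle test, and for the knee the last one would repeat a normalization already stated. The article is also condensed, and a fuller list of variables may exist elsewhere. What stands is that the text is at best ambiguous.

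**Relative strength is a legitimate target.** The Background itself names lower relative strength as a deficit of obese children and stresses tasks that move the body against gravity. Better strength for the load carried, reached through weight loss, is a real functional benefit. It would be wrong to call a per-kilogram gain spurious as such, or to say that torque per kilogram should be dropped or demoted. This objection stands in full. It leaves untouched the point that the ratio alone cannot show a gain in muscle strength.

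**Other measures remain.** A reader might infer that the trial would declare better neuromuscular function when only weight had changed. The documents do not support that. Proprioception, EMG latency and activation, the endurance index and ankle peak torque are also measured, no composite adds weight to strength, and body weight is reported separately.

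**The probabilities rest on assumptions.** This is correct. The highest figures need a high baseline correlation, efficient adjustment and no multiplicity correction, and the protocol foresees Bonferroni correction for post-hoc comparisons.

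**Conclusion.** The point holds with limited scope. On the most natural reading, knee strength is named only as torque per kilogram, while the ankle has both versions. The direction of the effect follows from the definition of the ratio and needs no assumption beyond a weight difference in favour of the programme. Its size depends on that difference, as shown above for 3%, 5% and 8%. For a 5% difference and a CV of 20%, the chance that it alone reaches significance at the uncorrected 5% level is roughly 30% to 66%, depending on baseline correlation and adjustment. None of these inputs is in the document.

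The severity is moderate to low: this is one secondary outcome among several neuromuscular measures, the wording leaves some doubt about what is intended, and the data needed to resolve it are already planned.

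**What to change.** State in the muscle strength section that absolute peak torque (Nm) will be analysed for the knee as well as the ankle, adjusted for baseline torque, and reported beside torque per kilogram for both joints. Keep torque per kilogram as a measure of strength relative to load. Add that a gain in muscle strength or neuromuscular function will be claimed from these tests only if absolute torque supports it.

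Dividing by fat-free mass is not an equivalent solution: diet and exercise may change that denominator too.

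The change costs wording only, since the dynamometer already yields absolute torque and no further measurement is needed. It is best made before outcome data are seen. The downside is that the strength result may look less favourable.

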**Figure 1 Fig1:**
[figure not shown]
**Flow diagram of study design.**

### Statistical analysis

Statistical analysis will be performed using SPSS for Windows version 17.0 (SPSS Inc. Chicago, IL). Data will be presented as the mean and standard deviation in which the distribution of variables is normal. Potential covariates will be determined at the baseline (that is, weight status, growth potential, sex, age, and socioeconomic status), and the difference by study groups or sex will be determined using one- or two-way analysis of variance or *χ*^2^ test. Baseline differences between those who attend and those who do not attend the follow-up measurements will be examined using separate variance *t* tests.

Intention-to-treat analysis will be performed by including all participants in the analysis according to the original group allocation. The follow-up will be maximized regardless of program attendance. A linear mixed model, which includes time (as a repeated factor), group, their interaction, and Bonferroni correction for *post-hoc* multiple comparisons, will be used to determine whether a significant time by group effect exists at the baseline, and after 6 months and 12 months. Average intervention effects of the follow-up period will be estimated and tested using the Bonferroni method for *post-hoc* analysis, in which groups by time interactions are insignificant.

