## Methods/design

### Study design

The study design is a single-blind randomized controlled trial that will compare a weight management program with health education. This study will be conducted at the Sport Medicine and Rehabilitation Center, Shanghai University of Sport. A total of 120 prepubescent obese children aged 8 to 10 years old will be included in the study. All participants will be recruited from a local primary school in Yangpu District, Shanghai, China. A multidisciplinary team composed of clinicians, dietitians, and exercise specialists will run the program.

Prior to initiation of the study, all subjects will complete a questionnaire that asks for details, such as medical history. The subjects will also complete the Mini-Mental State examination and Activity of Daily Living test, and describe their exercise habits (frequency and duration). Informed consent will be requested from all subjects and their parents prior to their inclusion in this study.

Participants who meet the inclusion criteria will be allocated in a 1:1 ratio by computer-generated randomization. After randomization, participants will be assigned to either the weight loss group or a health education group (control). This study will include assessments at the following time points: before intervention, after an intervention period of 6 months, and after a further follow-up period of 6 months with no active intervention. The total study period will be 12 months.

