### Outcome measures

All outcome measure assessments will be administered by the main research assistant, who will not be informed of the group allocation, at 2 weeks (baseline), 6 months (follow-up 1, at the end of the intervention), and 12 months (follow-up 2). A demographic questionnaire will be completed at baseline. Demographic information includes the participants’ and their parents’ characteristics (that is, sex, age, ethnicity, family structure, postcode, and socioeconomic status).

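### The stated mixed model treats baseline as a response and names no covariate; adjusting for baseline would be more precise at no cost, slightly for anthropometry and moderately for balance and neuromuscular outcomes

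*Protocol article*

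**What the plan says.** All of the analysis text is in the Statistical analysis section of the protocol article.

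- Covariates: "Potential covariates will be determined at the baseline (that is, weight status, growth potential, sex, age, and socioeconomic status"). The same sentence goes on to baseline testing: "the difference by study groups or sex will be determined using one- or two-way analysis of variance", or a chi-square test.
- Model: "A linear mixed model, which includes time (as a repeated factor), group, their interaction, and Bonferroni correction". None of the five listed covariates appears among its terms.
- Target of the test: the model "will be used to determine whether a significant time by group effect exists at the baseline, and after 6 months and 12 months". Baseline is thus one of three levels of the repeated factor, a response rather than a covariate.
- Fallback when the interaction is not significant: "Average intervention effects of the follow-up period will be estimated and tested using the Bonferroni method". How baseline enters that average is not stated.

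The timing of baseline is given in two ways. Outcome measures places the assessments "at 2 weeks (baseline), 6 months (follow-up 1, at the end of the intervention), and 12 months (follow-up 2"). Study design places them "before intervention, after an intervention period of 6 months, and after a further follow-up period of 6 months with no active intervention".

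**The concern.** The covariate list and the model are not joined up. Five covariates are named and their baseline differences are tested, yet the model uses none of them. The tests cannot help: allocation is random, so a difference between arms at baseline is chance, and its p-value says nothing about whether the covariate predicts the outcome.

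The strongest predictor of a 6-month value is usually the same child's baseline value. The plan uses it only by subtraction, through the time-by-group contrast. Subtraction gives baseline a coefficient of 1, whereas the best coefficient is the regression slope, which is below 1 whenever the measure is not perfectly repeatable. The cost is precision on every outcome. It is largest where repeatability is lowest, which is likely to be the balance and neuromuscular outcomes that give the trial its title and aim.

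Either use of baseline also needs one clear statement of when it is measured.

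**Working it through.** The article gives no alpha, power, effect size, standard deviation or correlation, so there is no figure of its own to reproduce.

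**Inputs.** From the article: 120 children allocated 1:1, so n = 60 per arm, measured at baseline, 6 and 12 months. Assumed: complete data, SD = 1 at every visit, equal correlation r between visits, and two-sided alpha 0.05 for power.

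**Variance of the estimated arm difference at one follow-up visit**

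- Raw difference at the visit: (2/n) × 1
- Difference in change (the time-by-group contrast): (2/n) × 2(1−r)
- Adjusted for baseline: (2/n) × (1−r²)

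Adjusted over change: (1−r²) / [2(1−r)] = (1+r)/2. Adjusted over raw: 1−r².

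| | r = 0.5 | r = 0.7 | r = 0.9 |
|---|---|---|---|
| SE, raw | 0.183 | 0.183 | 0.183 |
| SE, change | 0.183 | 0.141 | 0.082 |
| SE, adjusted | 0.158 | 0.130 | 0.080 |
| Variance, adjusted / change | 0.75 | 0.85 | 0.95 |
| Children giving the precision of 120 under change: 120 × (1+r)/2 | 90 | 102 | 114 |
| Power at an assumed 0.4 SD effect, change | 59.1% | 80.7% | 99.8% |
| Power at an assumed 0.4 SD effect, adjusted | 71.6% | 86.6% | 99.9% |
| Variance, adjusted / raw | 0.75 | 0.51 | 0.19 |

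**What happens to a chance baseline difference D between arms.** In theory the change estimate moves by −(1−r)D, the raw estimate by rD and the adjusted estimate by 0. A simulation with 6,000 runs per value of r agreed. At r = 0.5, 0.7 and 0.9 the slopes on D were −0.51, −0.30 and −0.10 for change, 0.49, 0.70 and 0.90 for raw, and about 0 for adjusted. For a chance difference of one standard error (0.183 SD), the change estimate shifts by 0.183 × 0.5 = 0.09, 0.183 × 0.3 = 0.05 and 0.183 × 0.1 = 0.02 SD, in the opposite direction to the imbalance. Averaged over randomisations, all three estimates are unbiased.

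**The average-effect fallback.** If this were a plain group effect over all three visits, the baseline visit would contribute no effect, and an assumed 0.40 SD effect would shrink to (2/3) × 0.40 = 0.27. With variance (2/n) × (1+2r)/3, power would be 43%, 37% and 33% at the three correlations. The article refers to the follow-up period and does not say that baseline is included, so this is a worst-case reading.

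**Baseline tests.** Five independent tests at 0.05 flag at least one difference with probability 1 − 0.95⁵ = 0.226 under correct randomisation. Independence and the 0.05 level are both assumptions.

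**The case against.** Three stronger readings are tempting, and the article does not support them.

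- *Baseline tests choose the covariates.* A reader might infer this because both statements share a sentence. But no rule admits a covariate on its p-value, and the verb used for the covariates can simply mean measured. The 22.6% figure would affect an estimate only if the tests did select covariates.
- *The outcome's own baseline is ignored, so chance imbalance stays in the result.* This is wrong for the stated test. The time-by-group contrast subtracts baseline, and what remains is over-correction by (1−r). Baseline as a repeated response is a recognised mixed-model form, and it keeps children with missing follow-up in the likelihood, in line with the intention-to-treat statement. The ratios of 0.51 and 0.19 are against a raw comparison at one visit, which is not the stated test.
- *Baseline is taken two weeks into the programme.* Nothing says so. The visit is labelled baseline, and Study design puts it before the intervention. The wording is unclear and needs an edit.

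It is also fair that a condensed article may leave the final covariate list to an analysis plan, that the list of model terms need not be exhaustive, and that the primary outcomes are body measurements, for which r may be high and the gain slight.

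What stands is that the article does specify a model and a test, that this test is less efficient than an equally simple alternative using data already collected, and that the covariate list has no stated role.

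**Conclusion.** The point holds as one of efficiency and clarity, not of validity. Against the stated time-by-group contrast, baseline adjustment removes 25%, 15% or 5% of the variance at r = 0.5, 0.7 or 0.9. If r is near 0.9 for weight, body mass index and body fat, the gain there is about 5% and hardly changes power. If r is 0.5 to 0.7 for postural and neuromuscular measures, the unadjusted contrast would need about 18% to 33% more children for the same precision (1/0.85 and 1/0.75). Matching these correlations to outcomes is an assumption, as the article reports none.

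The gain exceeds these figures only if the post-hoc or average-effect comparisons are plain group differences, and then only for r above 0.5. The article leaves that open.

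Between-arm baseline significance tests are uninformative whatever use is made of them. The two descriptions of baseline timing conflict as written and must be reconciled.

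**What to change.** 1. Model the 6- and 12-month values with the outcome's own baseline as a covariate, allowing its slope to differ by visit. Alternatively, keep baseline as a response and constrain the arm means to be equal there, which retains all randomised children with a baseline measurement.
2. Apply the same adjustment to the average-effect estimate, and state that it averages the 6- and 12-month effects only.
3. Name in advance which of the already collected covariates enter every model, for example sex and age. If baseline stays a response, let them interact with time: with complete data and equal correlations, a covariate entered only as a constant shift cancels out of the time-by-group contrast.
4. Describe the arms at baseline with summary statistics, and do not use between-arm significance tests to choose covariates.
5. Reconcile the baseline timing in Outcome measures with that in Study design.

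The cost is a few sentences in the protocol and analysis plan, agreed before outcome data are seen by arm. No further measurements or children are needed.

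### Testing an average effect whenever the group-by-time interaction is non-significant gives each outcome a second route to significance, with no alpha shared between the two steps

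*Protocol article*

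**What the plan says.** The Statistical analysis section of the protocol article describes the efficacy model as follows: "A linear mixed model, which includes time (as a repeated factor), group, their interaction, and Bonferroni correction for" post-hoc comparisons. The model is used "to determine whether a significant time by group effect exists at the baseline, and after 6 months and 12 months". Time therefore has three levels, and baseline is one of them. The outcome's baseline value is not named as a covariate in this model.

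A second step follows, in a sentence that opens "Average intervention effects of the follow-up period will be estimated and tested using the Bonferroni method for". The same sentence ends with the condition for taking that step, which is met by outcomes "in which groups by time interactions are insignificant".

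Bonferroni is named only for post-hoc comparisons. No significance level is given, and no sentence divides one between the interaction test and the average-effect test. On size, the Study design section says "A total of 120 prepubescent obese children aged 8 to 10 years old will be included in the study", allocated 1:1.

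**The concern.** With baseline inside the time factor, an intervention effect appears as the groups changing differently from baseline. That is the group-by-time interaction, on 2 degrees of freedom. Falling back to an average effect when the interaction is absent is a familiar step when time holds only post-treatment visits, because a missing interaction then means that the effect is steady over follow-up. Here a non-significant interaction means that the main test of the intervention has not rejected, and the rule then offers another test.

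Each outcome can therefore be declared positive in two ways. The rule belongs to the only between-group efficacy analysis the article describes, so the inflation recurs for each of the six primary outcomes and for every secondary one. If the average is a difference in raw means at follow-up, the second test also carries whatever baseline difference chance produced, and the write-up would call it an intervention effect.

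**Working it through.** **Inputs.** From the protocol: 120 children, 1:1, so 60 per arm; three visits; interaction test first; average-effect test if the first is not significant. Assumed: two-sided 0.05, since no level is stated; complete data; normal outcomes; within-child correlation 0.3 to 0.9, either equal between all visits or decaying with time (autoregressive). The protocol gives no error rate of its own to reproduce.

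**Step 1: arithmetic for raw means.** With equal correlations, the group difference averaged over all visits is independent of the interaction contrasts. The chance that at least one test rejects under no effect is

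1 − (1 − 0.05)(1 − 0.05) = 0.0975.

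If the second test uses 0.025: 1 − 0.95 × 0.975 = 0.0738. If both use 0.025: 1 − 0.975² = 0.0494.

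**Step 2: arithmetic for mean change from baseline.** This contrast lies inside the 2-df interaction, so the tests overlap. In large samples the extra rejections are those where the single contrast Z exceeds 1.96 in size but Z² plus the other component stays below the 2-df critical value of 5.99:

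0.05 + P(|Z| > 1.96 and Z² + X² < 5.99) = 0.05 + 0.025 = 0.075.

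**Step 3: simulation under no effect.** 200,000 trials per setting, 60 per arm, multivariate 2-df interaction test at 0.05, then a t test of the average at 0.05. The interaction alone rejected in 4.9 to 5.1%.

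| Meaning of the average effect | Total false-positive rate, second test at 0.05 | Second test at 0.025 (equal correlation 0.7) |
|---|---|---|
| Raw means, 6 and 12 months | 9.3–9.8% | 7.3% |
| Raw means, all three visits | 9.7–9.8% | 7.4% |
| Mean change from baseline | 7.5–7.6% | 5.5% |

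For raw means at 6 and 12 months, the lower end (about 9.3%) comes from the weakest correlations: 0.3, and 0.5 with decay. A separate run at correlations 0.5 to 0.9 put the raw-means readings at about 9.5 to 9.9% overall. If the standard deviation grows over time, the two raw-means figures are 9.1% and 9.3%. With 48 per arm (20% loss), the three rows are 9.8%, 9.8% and 7.5%.

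**Step 4: what drives the extra positives under raw means.** Take null trials that were significant only through the 6/12-month raw mean, with equal correlations of 0.5 to 0.9. The baseline group difference pointed the same way in 98 to 100% of them and averaged 0.26 to 0.39 SD.

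**Step 5: after the fix.** One prespecified contrast per outcome at 0.05, tested unconditionally, rejects in 5% under no effect.

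**The case against.** The strongest reply is that the size depends on a reading the text leaves open. The averaged quantity is an intervention effect over follow-up, and in this model that may naturally mean average change from baseline. The rate is then about 7.5%, or 5.5% with the second test at 0.025, and no uncorrected baseline difference remains. This stands. A flat statement that the rule nearly doubles the error rate describes only the raw-means readings.

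It is also fair that the second step can detect something real. A steady effect is better targeted by one averaged contrast than by a 2-df test: with a constant 0.35 SD effect and correlation 0.7, power was 81% for average change against 72% for the interaction. A reader might infer that the second test is run only when treatment has done nothing. Non-significance does not show that. The fault is the unallocated second test, not the averaged contrast itself.

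Three other stronger readings are not supported:

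- That averaging shrinks a constant effect to two thirds. This needs baseline in the average, whereas the sentence confines it to follow-up.
- That the raw follow-up comparison is biased. Under randomisation, chance imbalance is sampling error, and that test alone rejects at about 5%. What suffers is the total error rate and the interpretation of these particular positives.
- That the plan sets a separate group test at baseline. The phrase may simply list the visits in the model.

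Two defences of the rule do not remove the point. Bonferroni is not applied across the two steps, and with two groups an averaged effect is a single comparison, so the correction has nothing to divide. The baseline covariates listed in the same section, such as weight status, are compared by group or sex and are not entered in the mixed model.

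Finally, an unseen SAP may define the average and allocate alpha. The objection here is to a decision rule the article states, not to detail it omits.

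**Conclusion.** The point holds. Baseline is a level of time, the interaction already tests the intervention, and the stated fallback adds a second test without sharing alpha. Under two-sided 0.05 (assumed), 60 per arm and no true effect, the per-outcome false-positive rate is about 9.5 to 9.9% for raw means, slightly lower where correlation is weak or the spread grows, and about 7.5% for mean change from baseline. Using 0.025 for the second test alone leaves about 7.2 to 7.5% and 5.5%. Every reading exceeds 5%, and near-doubling is the top of the range. Reporting baseline imbalance as an effect is a risk only under the raw-means reading.

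**What to change.** - Model only the 6- and 12-month visits, with the outcome's baseline value as a covariate. Alternatively, keep all three visits and constrain the group means to be equal at baseline.
- Prespecify one between-group contrast per outcome, either the 6-month difference or the 6/12-month average, and test it whatever the interaction shows. The documents do not single out a time point, so the choice is the sponsor's.
- Report the remaining contrasts as secondary estimates with confidence intervals.
- Delete the rule that makes the average test depend on a non-significant interaction, and state the significance level.

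The cost is protocol and SAP wording only: no change to visits, measurements or sample size. Multiplicity across the six primary outcomes is a separate issue that this change leaves open.
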